### Economic evaluation

The result of this study is based on both the short-term and long-term success of surgical intervention and prolonged conservative treatment. The economic evaluation will be performed from a societal perspective. Both health care costs and costs of production losses will be included. Health care costs will include costs of general practice care, medical specialist care, physiotherapy, hospitalisation, medication and other costs directly associated with diagnosis, treatment and rehabilitation.

There are many variable parameters influencing the total costs of the surgical fixation (surgery time, extend of surgical fixation, systems used), which makes it very difficult to calculate the real costs of the surgical procedure. Therefore, real costs of surgery will not be estimated but based on standard prices in the participating hospitals. The costs of hospital admission in the surgical group will be calculated by the days spent on the Intensive Care Unit and the surgical department. Side-effects and complications related to the treatment are recorded by the patients, the treating surgeon or rheumatologist. The costs of complications will be reflected in additional intervention, prolonged duration of ICU stay and total admission time. The costs for re-surgery in the early surgery group and surgery in the conservative group will also be estimated.

In the study MRI and CT scans will be performed in both treatment groups. The costs of these imaging techniques will be included. The costs of the CT scan will only be calculated for patients undergoing surgery, because in the normal situation, CT would only be performed if a surgical indication exists. CT scans that are only used for research purposes will not be included.

Patients will register other health care needs in a diary (including physiotherapy, visits to GP's and specialists, nursing care and medication). Each diary covers a period of 3 months. The costs of health care will be assessed using standard prices. Patient/family costs and costs of production losses will also be collected in the cost diaries.

### Cost-effectiveness and cost-utility analysis

The aim of the economic evaluation will be to determine and compare the total costs for patients receiving surgery or conservative care, and to relate these costs to the effects of the interventions. The economic evaluation will be conducted from societal perspective and will be carried out according to the intention-to-treat principle. Bootstrapping will be used for pair-wise comparison of the mean differences in total costs between the intervention groups. Confidence intervals will be obtained by bias corrected and accelerated (Bca) bootstrapping using 2000 replications.

Cost-effectiveness ratios will be calculated by dividing the difference in mean costs of the two interventions by the difference in mean effects of the two interventions. Ratios will include the primary clinical effect measures of the trial. Cost-utility ratios will also be calculated. Ratios will be graphically presented on cost-effectiveness and cost-utility planes. Acceptability curves will also be presented.

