## Design

An international multicenter randomized clinical trial will be performed. Centers in the Netherlands (table 1), Belgium, Denmark, France, Germany, Italy, Latvia, Portugal, Spain, Sweden, Switzerland, United Kingdom, USA and Canada will participate (table 2 and figure 1 and 2). The multicenter design is necessary to recruit all patients in the inclusion period of 2 years. Early surgery will be compared with prolonged conservative treatment. The selection and randomization procedure is depicted in figure 3. The overall range for randomization of the AAS is an AADI between 5–12 mm. Participating centers/countries are allowed to randomize different intervals of subluxation. The intervals are predefined as 5–8 mm, 5–12 mm and 8–12 mm. Demographic and clinical data will be collected of each patient. The randomization of all patients will be performed centrally at the LUMC by the trial coordinator and datamanager by a concealed randomization list in random permuted blocks.

After a follow up of 5 years the main research question will be answered, although the total follow-up will be 10 years. Patients excluded from the trial will be followed in a cohort group and treated according to the usual care by surgical fixation or conservative treatment. The LUMC will function as the research and data coordinating center, where the data will be collected, analyzed and publications prepared. Eligibility criteria will differ from site to site, according to local perceptions of equipoise. These efforts will increase the generalization of the results. The authors have full access to the data, direct the data-analysis and are responsible for decisions regarding publication. The principal investigator and the trial coordinator assume full responsibility for the integrity and interpretation of the data.

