#### Secondary outcome parameters

1) 'Perceived recovery/deterioration.' This is a seven-point Likert scale measuring the perceived recovery or progression, varying from 'completely recovered' to 'worse than ever'.

2). The American Spinal Injury Association (ASIA) and International Medical Society of Paraplegia have developed a standard form for capturing clinical information when evaluating a patient who has had a spinal cord injury. The ASIA score is a motor and sensory quantifying score of both arms and legs [46]. The ASIA score will be used once neurological deficits have occurred.

3). The Disease Activity Score (DAS-28) is a classification used by many rheumatologists and is a measure of the overall disease activity of RA. In Europe the DAS is the recognized standard in research and clinical practice. For a good comparison of the severity and disability due to the RA inflammatory process between all patients in the two treatment groups of the different countries the DAS-28 will be used. The following parameters are included in the calculation: Number of joints tender to touch (TEN), Number of swollen joints (SW), Erythrocyte sedimentation rate (ESR), patient assessment of disease activity [47].

4). VAS pain will be measured of pain in the neck and occiput before randomization and during the follow up. Pain will be assessed on a horizontal 100 mm scale varying from 0 mm, 'no pain', to 100 mm, 'the worst pain ever' [48].

5) EuroQol classification system and VAS rating personal health [49]. A cost-utility analysis will be performed using QALY's based on the EuroQol questionnaire, which has been validated in many studies and is easy to fill out. Patients describe their general health status using the EuroQol classification system, consisting of 5 questions on mobility, self care, usual activities, pain/discomfort, and anxiety/depression. Patients also rate their personal health using a visual analogue scale (VAS) ranging from worst imaginable health to best imaginable health.

6) Short-Form 36 (SF-36). Quality of life will also be assessed using the RAND-36 questionnaire [50]. This is a generic health status questionnaire, which can easily be filled out at home. The questionnaire consists of 36 items on physical and social functioning.

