### Follow up

Follow up with clinical assessments and outcome measures will be assessed at baseline and after 3, 6, 12, 18 and 24 months. After two years the patient will be controlled once a year till eventually 10 years after randomization. During the follow up parameters will be registered to evaluate the quality of life, illness restrictions and neurological impairments. Direct and indirect medical costs will be calculated in each group.

Every control moment an X-ray of the cervical spine will be made (neutral/flexion/deflexion) except three months postoperatively. Prior to randomization and six months postoperatively a CT scan will be made to evaluate fusion and surgical stabilization. At fixed intervals and on clinical indication a MRI scan of the cervical spine will be performed. The clinical, neurological and radiological parameters will be registered on the follow up CRF. Data collection will take place per treatment center and will be gathered and analyzed at the LUMC in Leiden by the trial coordinator together with the statistical department and the epidemiological department of the VUMC in Amsterdam.

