### Statistical analysis

The researchers will be aware of allocation to early surgery or conservative treatment at the time of the statistical analyses. There will be an intermediate analysis after 2 years of follow up. The intermediate outcome measures are progression of AAS and VT with or without (pain) complaints and neurological disability (measured with the MDI and Ranawat). The main analyses will be performed after 5 years and 10 years of follow up. At these intervals the primary outcome parameter is the occurrence of an event as described in table 5. Baseline comparability will be investigated by descriptive statistics to examine if randomization was successful. Differences in success rates between both groups are calculated, together with 95 percent confidence intervals. In addition to an analysis of the difference in outcome between the two groups analyses of the difference in time to progression will be carried out. Continuous outcomes are evaluated as change scores (differences between baseline measurement and each follow-up measurement). Multivariable analyses are performed to adjust for the eventual differences between the groups at baseline in prognostic indicators. All the analyses are performed according to the intention-to-treat principle. An additional per protocol analysis will be performed comparing patients in the conservative group who received surgery with patients in the same group who had not and with patients in the surgery group. To compare the actual treatment sec instead of strategies an explorative analysis will be performed in subgroups of all patients who actually received surgery and who did not receive surgery in both groups. All patients withdrawn from the study are included in the analysis until the time of withdrawal.

To answer the third research question, explorative analyses are conducted to investigate whether the treatment effect varies in specific subgroups of patients. Using logistic regression for success rate and linear regression for severity of the disability, each prognostic indicator is checked for interaction with treatment.

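### The cost-utility comparison is defined as a difference in arm means and makes no stated use of the baseline EuroQol utility, which would sharpen it at no cost

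*Protocol article*

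**What the plan says.** Cost-effectiveness is the second of the two main questions under Main research questions. The section Cost-effectiveness and cost-utility analysis obtains ratios by "dividing the difference in mean costs of the two interventions by the difference in mean effects of the two interventions". For QALYs it adds only that "Cost-utility ratios will also be calculated". It specifies intention-to-treat, BCa intervals with 2000 replications, planes and acceptability curves. The bootstrap is named for costs: "Bootstrapping will be used for pair-wise comparison of the mean differences in total costs between the intervention groups". No covariate is mentioned.

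Under Secondary outcome parameters, "A cost-utility analysis will be performed using QALY's based on the EuroQol questionnaire". Under Follow up, "Follow up with clinical assessments and outcome measures will be assessed at baseline and after 3, 6, 12, 18 and 24 months", then yearly, so a baseline utility will be on file.

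Two sentences under Statistical analysis bear on baseline values: "Continuous outcomes are evaluated as change scores (differences between baseline measurement and each follow-up measurement"), and "Multivariable analyses are performed to adjust for the eventual differences between the groups at baseline in prognostic indicators". Neither mentions QALYs or the EuroQol, and the economic section does not refer to either.

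No horizon is given for the QALYs. The Design section says: "After a follow up of 5 years the main research question will be answered, although the total follow-up will be 10 years".

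**The concern.** A QALY total is the area under a patient's utility curve, and that curve starts at the baseline utility. Patients with a chronic disease who start low tend to stay low. A chance difference between arms at baseline therefore tends to recur at later visits and accumulates in the QALY difference, which is the denominator of the cost-utility ratio. Regression on baseline utility removes the predictable part of that carry-over and narrows the interval.

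The change-score rule is no substitute. A QALY total has no baseline value of its own to subtract. Subtracting horizon times baseline utility assumes that the baseline persists in full, and this can give a larger standard error than no adjustment.

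At stake is the precision of the cost-utility plane and acceptability curve, and how far they reflect a chance difference at entry.

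**Working it through.** The plan states no figure for the QALY analysis, so there is none to reproduce. The check asks what baseline adjustment would gain.

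**Inputs from the protocol article:** 250 patients and 20% loss per arm (Sample size/power calculation); visits at 0, 3, 6, 12, 18 and 24 months, then yearly (Follow up).

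**Assumptions, not in the document:** 1:1 allocation, so 125 per arm; EuroQol at every visit; utility SD 0.27 at each visit; a 5-year horizon; complete data; correlation ρ between single visits of 0.3 to 0.7.

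**Step 1, weights.** The trapezoid rule over 0, 0.25, 0.5, 1, 1.5, 2, 3, 4 and 5 years gives weights 0.125, 0.25, 0.375, 0.5, 0.5, 0.75, 1, 1 and 0.5. They sum to 5, and their squares sum to 3.531.

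**Step 2, chance imbalance.** The SE of the baseline difference is 0.27 × √(2/125) = 0.034.

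**Step 3, constant correlation.**
- Slope of QALY on baseline: b = 0.125 + 4.875ρ.
- QALY variance in units of SD²: V = 25ρ + 3.531(1 − ρ).
- Share of variance removed by regression: b²/V.
- SE unadjusted: 0.034 × √V. SE adjusted: 0.034 × √(V − b²).
- Shift from a one-SE imbalance: 0.034 × b.

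| ρ | b | V | variance removed | SE unadjusted | SE adjusted | one-SE shift |
|---|---|---|---|---|---|---|
| 0.3 | 1.59 | 9.97 | 25% | 0.108 | 0.093 | 0.05 |
| 0.4 | 2.08 | 12.12 | 36% | 0.119 | 0.095 | 0.07 |
| 0.5 | 2.56 | 14.27 | 46% | 0.129 | 0.095 | 0.09 |
| 0.6 | 3.05 | 16.41 | 57% | 0.138 | 0.091 | 0.10 |
| 0.7 | 3.54 | 18.56 | 67% | 0.147 | 0.084 | 0.12 |

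**Step 4, decaying correlation.** The weights are the same, but the correlation between two visits falls with the time between them.
- Starting at 0.5 and falling 20% a year: 23% of variance removed, shift 0.05.
- Starting at 0.7 and falling 30% a year: 24%, shift 0.06.
- Starting at 0.7 and falling 10% a year: 48%, shift 0.09.
- Purely geometric, 0.4 to 0.7 per year: 14 to 37%, shift 0.04 to 0.08.
- Weakest case tried, starting at 0.3 and falling 30% a year: 9%, shift 0.03.

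**Step 5, the change-score alternative.** For QALY minus 5 × baseline, the SE is 0.034 × √(V − 10b + 25). At constant ρ = 0.4 this is 0.034 × √16.37 = 0.138, against 0.119 unadjusted and 0.095 with regression.

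**Step 6, losses.** With 100 per arm, SEs and shifts grow by √(125/100) = 1.12. The percentage of variance removed does not change.

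**The case against.** The strongest reply is that this is silence in a condensed article. The ratio formula is the standard definition, a regression-adjusted mean difference satisfies it equally well, and the text never calls its means raw or unadjusted. QALY covariates usually belong to a statistical or health-economic analysis plan, which is not shown. The multivariable sentence under Statistical analysis is not limited to clinical outcomes and might be meant to cover QALYs. Much of this stands. A reader might infer that the plan prescribes unadjusted QALYs; the wording does not go that far. What remains is that the section gives a formula built on arm means, offers nothing else for the cost-utility ratio, and does not link to an adjustment that itself lists no covariates. The researchers will also know the allocation at analysis, which favours naming the covariate in advance.

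The second reply is that randomisation makes the unadjusted difference unbiased, and that bootstrap spread already includes chance imbalance. This stands in full. A reader might infer a biased analysis; there is none.

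The third is that the size rests on assumed inputs. This also stands: no utility SD, correlation or QALY horizon is given.

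A reader might also infer that a chance imbalance could be as large as the treatment effect, because the expected event rates differ by only 8% − 2% = 6 percentage points. The documents do not support that. They give no QALY effect, and peri-operative morbidity and loss of neck rotation would affect QALYs across the surgical arm, so the effect cannot be read from the event gap.

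**Conclusion.** The point holds as a recommended improvement, not as an error in the plan. As written, the cost-utility comparison makes no stated use of a baseline measurement that the trial already collects, and neither baseline sentence under Statistical analysis clearly fills the gap. The consequence is avoidable loss of precision, with chance imbalance left in the QALY difference.

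Under SD 0.27, 125 per arm, a 5-year horizon and between-visit correlation of 0.3 to 0.7, adjustment removes roughly 20 to 67% of the variance, and a one-SE imbalance moves the unadjusted difference by about 0.05 to 0.12 QALY. Weak correlation that fades quickly takes both figures lower, to 9% and 0.03 in the weakest case tried. The direction is the same in every case; the size cannot be fixed from the documents.

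**What to change.** In Cost-effectiveness and cost-utility analysis, state that the QALY difference is estimated by regression on treatment arm and baseline EuroQol utility. State also that this adjusted difference is bootstrapped jointly with the cost difference, resampling patients so that costs and QALYs stay paired, and that the ratio, planes and acceptability curves are built from those replicates. Keep the unadjusted difference as a sensitivity analysis. If a separate analysis plan already says this, a cross-reference is enough.

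The cost is a sentence or two of text. No extra patients, visits or data are needed.

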## Discussion

### Ethical considerations

Is it fair to perform a surgical cervical fixation on patients with rheumatoid arthritis with atlantoaxial pathology without neurological complaints? From the literature it is not known which treatment is preferable. Advantages of early surgery are probable preservation of neurological functions with a higher degree of general functioning. The surgical fixation will be less extensive and easier to perform compared to surgery in a later stage, because of the more pronounced destruction of the joints and bones. If neurological deficits are present before surgical fixation, there is little chance of (full) neurological recovery. The large variability in the progression of AAS, eventually resulting in neurological deficits, makes it hard to determine the right timing for surgical fixation. It can take years before patients get neurological complaints or deficits. Another disadvantage is that with surgery in an earlier phase of AAS more patients have to be operated on. After surgical fixation, patients are more restricted in their head and neck movements. In turn, it must be noted that limited neck range of motion already exists in 90% of patients with RA. The overall conclusion is that it is fair to practice surgical fixation before the onset of neurological signs and symptoms in patients with significant AAS.

## List of abbreviation

AAS: Atlanto Axial Subluxation

ASIA: American Spinal Injury Association

AADI: Anterior Atlanto Dental Interval

CT: Computer Tomography

DAS: Disease Activity Score

DMARD: Disease Modifying Anti Rheumatoid Drugs

MDI: Myelopathy Disability Index

MRI: Magnetic Resonance Imaging

PADI: Posterior Atlanto Dental Interval

RA: Rheumatoid Arthritis

SF-36: Short Form 36

SAS: Subaxial Subluxation

VAS: Visual Analogue Scale

VT: Vertical Translocation
